**Fig. 1 Fig1:**
[figure not shown]
Flow chart of the EUROPA trial. POD, postoperative day; PD, partial pancreatoduodenectomy

#### Analysis variables and statistical methods

The primary endpoint is the CCI within 90 days after the intervention. As a primary result, the 95% CI for the difference in the means between the two groups will be reported. Since the CCI is approximately normally distributed [25], the 95% CI can be computed by means of the normal distribution. Further descriptive measures are reported in terms of mean and standard deviation.

Data analysis will be based on three analysis sets. The intention-to-treat (ITT) set comprises all patients in the group to which they were randomised (converted patients remain in the RPD group) and serves as the primary analysis set. Patients that receive an operation other than PD or total pancreatectomy (explorative laparotomy, diagnostic laparoscopy, etc.) are excluded from further analysis and proceed directly to the end-of-study visit (V8). The per-protocol (PP) set consists of all patients treated per protocol without major protocol violation and without conversions. No missing data will be imputed in the PP set. In addition, the as-treated set will be analysed, which considers the patients in the group in which they were finally treated (i.e. converted patients in the OPD group). There is no evidence that the converted patients will have a higher postoperative CCI than those patients randomised to and remaining in the OPD group. Therefore, and due to the exploratory character of this trial, the as-treated set is an important complement to the ITT and PP sets in this trial.

The primary endpoint is expected to be missing for a small number of patients, since it is objective and short term. In these cases, the primary endpoint is imputed using mean imputation based on the treatment group. As sensitivity analyses, worst-case and best-case scenarios are investigated. Missing values of the primary endpoint will be imputed using the lowest and the highest value of the corresponding treatment group.

The secondary endpoints are described as mean values along with standard deviations, median values, quartiles, minimum and maximum for continuous endpoints, and relative and absolute frequencies for categorical endpoints, stratified for treatment groups. Effect sizes (mean difference for continuous data, Hodges–Lehman estimator for scores and risk difference for binary data) including 95% CIs will be reported. The safety analysis includes calculation of frequencies and rates of both minor (Clavien–Dindo class I and II) and major complications (Clavien–Dindo class III to V) together with 95% CIs. Statistical methods will be used to assess the quality of data and the homogeneity of the intervention groups.

Details of statistical analyses as well as the handling of potential data problems will be defined in a statistical analysis plan (SAP) prior to database closure.

All analyses are exploratory, having only descriptive character, and will be conducted using SAS version 9.4 or higher.

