## Background

By 2030, pancreatic cancer is expected to be the second leading cause of cancer-related deaths in the USA [1]. Each year, 610,000–915,000 quality-adjusted life-years are lost to pancreatic cancer in Europe [2], dramatically impairing the quality of life of patients and caregivers. Surgical resection offers the only chance of long-term survival. Partial pancreatoduodenectomy (PD) is the indicated surgical procedure for pancreatic head cancer and for a wide range of benign and other malignant diseases of the pancreas and distal bile duct.

Advances in surgical technique and perioperative care have decreased the perioperative mortality of pancreatic resection to below 5% at specialised high-volume centres. Perioperative morbidity, however, remains high, with rates around 40% [3]. Therefore, measures to reduce postoperative complications are urgently needed. Minimally invasive surgery has been shown to decrease postoperative morbidity in a wide range of surgical indications. Laparoscopic PD was introduced in 1994 [4] and robotic PD (RPD) in 2003 [5]. Several small, non-randomised and mostly retrospective and single-centre studies and case series have investigated RPD and compared it with open PD (OPD), with inconsistent results [6–14]. While the operating time was longer for RPD in most studies [6, 8, 9, 12, 15], comparable positive margin rates [11] and similar incidences of postoperative haemorrhage [10] were reported. While some studies found a higher number of harvested lymph nodes [9, 13], lower blood loss [7–9, 12, 13, 15] and fewer major complications for RPD [7], other studies reported the contrary, with higher margin positivity [6] and fewer harvested lymph nodes for RPD [6]. A meta-analysis of the limited data derived from a small number of mainly observational studies revealed the superiority of RPD for three efficacy outcomes: wound infection rate, margin positivity rate and length of hospital stay [16].

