### Primary and secondary endpoints

The primary endpoint of the EUROPA trial is cumulative morbidity within 90 days after PD, assessed by means of the CCI. The CCI is based on the established Clavien–Dindo classification of postoperative complications, which has gained widespread acceptance [24]. The Clavien–Dindo classification grades postoperative complications according to their sequelae, ranging from grade I (any deviation from the normal postoperative course without the need for pharmacological treatment) to grade V (death). The CCI score ranges from 0 (no complication of any kind during the postoperative course) to 100 (death of patient). The CCI permits objective assessment of cumulative postoperative morbidity even in an unblinded study setting. The CCI was developed jointly by surgeons and patients and considers the patient’s perspective as well as objective parameters of surgical effectiveness [25]. It is validated for the pancreatic surgical population and a difference of 10 is regarded as clinically relevant [26].

The secondary endpoints cover important oncological, clinical, economic and patient-relevant outcomes (Table 1).

**Table 1 Tab1:** Definition of secondary endpoints

Secondary endpoint	Definition
General outcomes	
Feasibility of recruitment	Recruitment goal of *n* = 80 patients within 18 months.
Costs (€)	Procedure-related costs and all inpatient hospital costs up to POD 90.
Intraoperative outcomes	
Duration of surgery (min)	RPD: from the start of positioning of the robot to the end of skin closure. OPD: from the beginning of skin incision to the end of skin closure.
Blood loss (ml)	As recorded in the anaesthesiology report.
Serious intraoperative complications	Any untoward medical/surgical occurrence that results in death, is life-threatening, requires prolongation of existing hospitalisation or results in persistent or significant disability/incapacity. Intraoperative in this context is defined as from the beginning of anaesthesia until the end of skin closure.
Conversion rate (%)	Conversion rate from robotic to open surgery.
Surgeon’s mental workload/stress	Self-evaluation according to the National Aeronautics and Space Administration Task Load Index [27] at the end of surgery.
Oncological outcomes	

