### Statistics

#### Sample size calculation

Given that EUROPA is an exploratory trial, no formal sample size calculation was performed. However, a clinically relevant mean difference for the CCI is 10 [25, 26] while the mean standard deviation is approximately 20 in major abdominal surgery [38]. Including 64 patients (32 per group) in the analysis, this effect size could be estimated with a 95% confidence interval (CI) of [3.07, 16.93]. Considering that approximately eight patients per group will undergo neither RPD nor OPD due to inoperability or indication for another type of surgery (ascertained during the exploratory stage of the operation), a total of 80 patients will need to be allocated to the trial (Fig. 1).

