No competing clinical trial has been identified in any of the following clinical databases: ClinicalTrials.gov, Current Controlled Trials, University Medical Information Network (UMIN) Clinical Trials Registry and German Clinical Trials Register (DRKS).

One RCT comparing minimally invasive surgery (either laparoscopic (*n* = 42 patients) or robotic (*n* = 5 patients)) with open surgery (Dutch Trial Register, NTR5689) was terminated early due to high mortality in the minimally invasive group [29]. However, RPD was underrepresented in this trial, and laparoscopic and robotic PD are not equivalent in terms of risks, complications or costs. Collective evaluation of the two strategies would distort a number of critical endpoints and is not meaningful, as the robotic approach clearly differs from laparoscopic PD. Accordingly, a valid conclusion about RPD cannot be drawn from this trial due to the very low proportion of patients that underwent RPD.

The available data on overall morbidity rates are heterogeneous (RPD 25–76% and OPD 40–75%) [7–9, 14, 21]. Study populations and definitions of endpoints were heterogeneous or were not sufficiently defined in previous studies. In addition, the learning curve of participating surgeons was addressed in only some of the studies [6, 12]. Furthermore, data on long-term results and cost-effectiveness are lacking.

The current vivid discussion on robotic surgery addresses cost-effectiveness issues in most cases. However, sound-randomised evidence for surgical and oncological effectiveness as well as safety are rarely available, which hampers these scientific discussions. This trial is the first step to establish high-level evidence on efficacy and safety for RPD as a required basis for a future assessment of cost-effectiveness.

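### The claim that the CCI is approximately normal should be dropped and the primary 95% CI taken from the t distribution; as written, the interval is about 2% too short

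*Protocol article*

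**What the plan says.** In the protocol article, section Analysis variables and statistical methods, the primary analysis is set out as follows: "As a primary result, the 95% CI for the difference in the means between the two groups will be reported". The method comes next: "Since the CCI is approximately normally distributed [25], the 95% CI can be computed by means of the normal distribution". Beyond the interval, the primary endpoint is summarised by mean and SD. For continuous secondary endpoints the same section adds median, quartiles, minimum and maximum, and for scores a Hodges–Lehmann estimate.

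The other relevant statements are:

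- Primary and secondary endpoints: "The CCI score ranges from 0 (no complication of any kind during the postoperative course) to 100 (death of patient").
- Background: "Perioperative morbidity, however, remains high, with rates around 40" per cent.
- Discussion: "The available data on overall morbidity rates are heterogeneous (RPD 25–76% and OPD 40–75" per cent).
- Sample size calculation: "a clinically relevant mean difference for the CCI is 10", "the mean standard deviation is approximately 20 in major abdominal surgery", and "Including 64 patients (32 per group) in the analysis".

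The article calls all analyses exploratory and descriptive and leaves details to a statistical analysis plan, which is not shown.

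**The concern.** The method is justified by a distributional statement that fits poorly with the article's own description of the score. A scale that stops at 0 and 100, with every uncomplicated patient at 0 and every death at 100, should show a spike at 0 and a long right tail.

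Two things could be at stake. The first is the coverage of the primary interval, which is the trial's main result. The second is the description of the endpoint. The Discussion says the morbidity data should support the sample size of a confirmatory trial on the same CCI. In a group of 32, one patient at 100 in place of 0 moves the mean by 100/32 = 3.1 points, almost a third of the difference called clinically relevant. A mean and an SD alone do not show the shape behind such shifts.

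**Working it through.** **Inputs.** From the article: difference 10, SD 20, 32 analysed per group, scale 0 to 100, morbidity about 40% (Background), 25–76% for RPD and 40–75% for OPD (Discussion). Assumed: that morbidity means any complication (CCI above 0), the mean CCI values in step 3, and the severity mixes in step 5.

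**1. The plan's own interval.** The section Sample size calculation gives [3.07, 16.93], a half-width of (16.93 − 3.07)/2 = 6.93. Then 6.93/1.96 = 3.536 = 20/√32. The quantile used there is therefore 1.96, which supports reading the analysis sentence as meaning the normal quantile. The standard error of 3.536 is not the two-sample value for 32 per group, which is 20 × √(2/32) = 5.00. That is a separate matter and does not enter here; the steps below use 5.00.

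**2. Patients at 0.**

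| Source | Morbidity | Share at CCI 0 |
|---|---|---|
| Background | about 40% | about 60% |
| Discussion, RPD | 25–76% | 24–75% |
| Discussion, OPD | 40–75% | 25–60% |

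**3. What a normal curve would imply.** With SD 20, the share below 0 is Φ(−mean/20). The article gives no mean CCI. For assumed means of 10, 20 and 30 the share is 31%, 16% and 7%, on a scale where no value below 0 exists.

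**4. Effect of the quantile.** Half-width = quantile × 5.00.

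- Normal: 1.960 × 5.00 = 9.80, interval [0.20, 19.80].
- t with 62 degrees of freedom: 1.999 × 5.00 = 9.995, interval [0.01, 19.99].
- Ratio: 9.995/9.80 = 1.02.

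If the data were exactly normal, the z interval would cover P(|t62| ≤ 1.960) = 94.55%.

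**5. Effect of the skewness.** Two sets of simulated CCI-like outcomes were run with 32 per group.

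- *First set* (200,000 trials per scenario): morbidity pairs between 25% and 76%, 5% of patients with complications at 100, skewness about 1.1 to 2.6, SD 18.7 to 24.1. The z interval covered 94.6–94.8% and the Welch t interval 95.1–95.5%. Exactly normal data in the same program gave 94.5% for z.
- *Second set* (40,000 trials per scenario): zeros/deaths of 60%/3%, 40%/3% and 25%/5%. The z interval covered 94.4%, 94.6% and 94.5%; Welch covered 95.1%, 95.1% and 95.0%.

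The z interval therefore does no worse with skewed, zero-heavy data than with normal data. The shortfall comes from the quantile. With two equal groups of 32, skewness adds no measurable loss.

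**The case against.** **The loss is trivial in a descriptive trial.** No test or decision depends on half a point of coverage. This stands, and it sets the severity.

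**The sentence may mean a normal-theory interval, of which the t interval is the usual form, and the choice is a detail for the analysis plan.** This stands in part. The wording is open, and the analysis plan may already use t. But the article states both a method and a reason for it, and its planning interval uses 1.96.

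**The cited morbidity rates may not mean CCI above 0.** This is fair. The Discussion itself says endpoint definitions in those studies were heterogeneous or insufficiently defined, and any recorded grade I deviation lifts the CCI above 0. If minor events were left out of the cited rates, fewer patients sit at 0 and the conflict is weaker. The bounds at 0 and 100 remain.

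**A reader might infer that non-normality invalidates the primary interval.** The documents do not support this. The target is a difference in means, which does not need normal patient data at this size, and step 5 finds no harm from skewness.

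**A reader might also infer that mean and SD would hide an effect driven by a few deaths.** They are not the only information planned. Mortality to day 90 is a secondary endpoint, and rates of minor and major complications are reported with 95% CIs. What is not named is the CCI's own median, quartiles and range, and the proportion at 0.

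**Rank-based summaries are no cure.** With about 60% zeros the median is 0. With 60% against 40% zeros and equal severity among patients with complications, pairwise differences are 48% in one direction, 24% tied at zero (0.6 × 0.4) and 28% in the other. The Hodges–Lehmann estimate is then 0 despite a 20-point difference in complication rate. This stands, so that estimate is optional.

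**Conclusion.** A minor point that is wrong as written. The statement that the CCI is approximately normal is unlikely to hold, given the scale and the cited morbidity rates, and the analysis does not need it. Read as the normal quantile, the method makes the primary interval about 2% too short: 9.80 against 9.995 at SD 20, with coverage of about 94.5% instead of 95%. The primary endpoint is also described less fully than the secondary ones.

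The size of the quantile effect rests only on 32 per group and an estimated SD. The share of patients at 0 rests on reading morbidity as any complication. The finding that skewness is harmless rests on assumed severity mixes, but two different mixes agree. None of this makes the mean difference the wrong target or the interval seriously misleading.

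**What to change.** In the section Analysis variables and statistical methods:

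1. Delete the statement that the CCI is approximately normally distributed.
2. State that the primary 95% CI for the difference in means is computed with the Welch t distribution.
3. Report median, quartiles, minimum and maximum for the primary CCI, as already planned for continuous secondary endpoints, and add the proportion of patients with CCI 0 in each group.

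Deaths and minor and major complication rates are already planned. A Hodges–Lehmann estimate or a bootstrap interval for the CCI may be added but is not needed. The cost is one rewritten sentence, a few lines of code and an interval about 2% wider; the target of estimation does not change. If the analysis plan already specifies a t interval, only the article's wording needs to be aligned.

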### Withdrawal criteria

Participants may withdraw from the trial at their own request at any time without giving reasons. If PD cannot be performed (e.g. because of technical irresectability or metastatic disease), the patient concerned will leave the trial early. The latter category will be included in the final report of the trial to ensure complete transparency.

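### The primary set is labelled intention-to-treat but leaves out an expected 20% of randomised patients, and the protocol is not consistent on who they are or clear on whether they are followed

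*Protocol article*

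**What the plan says.** In the Protocol article, Analysis variables and statistical methods, the ITT set is the primary analysis set and "comprises all patients in the group to which they were randomised"; patients converted from robotic to open surgery stay in the robotic group. The exclusion rule follows: "Patients that receive an operation other than PD or total pancreatectomy (explorative laparotomy, diagnostic laparoscopy, etc.) are excluded from further analysis". The same sentence sends these patients straight to V8, which Table 2 places at POD 90.

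Sample size calculation plans for the loss: "approximately eight patients per group will undergo neither RPD nor OPD due to inoperability or indication for another type of surgery", with the reason "ascertained during the exploratory stage of the operation". Hence "a total of 80 patients will need to be allocated to the trial", and the precision statement begins "Including 64 patients (32 per group) in the analysis". The abstract gives the same counts.

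Withdrawal criteria words the rule differently: "If PD cannot be performed (e.g. because of technical irresectability or metastatic disease), the patient concerned will leave the trial early". It adds that these patients will appear in the final report.

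Patients are randomised before surgery (Assignment of intervention and randomisation; visit 1 in Table 2). Operating surgeons and outcome assessors cannot be blinded (Postoperative data collection and blinding).

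**The concern.** An ITT set keeps every randomised patient in the assigned arm, so that the comparison rests on randomisation. The set described here is restricted by something learned after randomisation, during an operation led by a surgeon who knows the allocation. If the judgement that a tumour cannot be resected differs between arms, the patients kept in the two arms may no longer be comparable. Equal numbers excluded would not rule this out.

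The exclusion is from further analysis in general, so on its wording it applies to the per-protocol and as-treated sets too. No stated analysis covers all 80 patients. The imputation rule does not fill the gap: it is meant for a few missing endpoints, whereas these patients are removed by definition.

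The differing descriptions raise a practical problem. If site staff cannot tell who is excluded and whether 90-day complications are to be recorded for them, an all-randomised analysis may not be possible later.

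**Working it through.** **1. The plan's own figure.** Inputs from Sample size calculation: 80 allocated, 64 analysed, about 8 lost per group.
- Share excluded: (8 + 8)/80 = 16/80 = 20%.
- Inflation: 64/(1 − 0.20) = 80.

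The stated 80 is reproduced exactly, so the planned primary analysis is of 64 patients, not of all randomised.

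**2. Who is excluded.**
- Analysis section: any operation other than PD or total pancreatectomy. Total pancreatectomy is kept.
- Withdrawal criteria: anyone in whom PD cannot be performed. Total pancreatectomy is not excepted.
- Sample size calculation: anyone who has neither RPD nor OPD, including those needing another type of surgery. Total pancreatectomy is not excepted.

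Read literally, the last two drop a patient whom the first keeps.

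**3. Whether they are followed.**
- Withdrawal criteria: they exit the trial early.
- Analysis section with Table 2: they go to V8, at POD 90, where the CCI is among the scheduled assessments.
- Sample size calculation: silent.

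The text does not settle whether V8 here means a POD 90 contact or an immediate close-out.

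**4. Illustration of selection (assumed inputs, no true effect).** Suppose the decision removes k more of 32 patients from one arm, and their mean CCI is g points above that of the patients kept. The mean of those kept then lies k·g/32 below the mean of all 32.
- k = 1, g = 5: 1 × 5/32 = 0.16 points.
- k = 2, g = 10: 2 × 10/32 = 0.62 points.
- k = 4, g = 20: 4 × 20/32 = 2.5 points.

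The clinically relevant difference in the plan is 10.

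**5. What an all-randomised analysis would estimate (assumed inputs).** With 20% excluded in each arm and a difference of 10 in those analysed, the all-randomised difference is 0.8 × 10 + 0.2 × d, where d is the difference among those excluded.
- d = 0: 8.0.
- d = −10: 6.0.
- d = +10: 10.0.

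**6. Precision (SD 20 from the plan, two-sample normal formula).**
- 32 per group: 1.96 × 20 × √(2/32) = 9.80.
- 40 per group: 1.96 × 20 × √(2/40) = 8.77.

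The second figure assumes that the SD stays at 20 once non-resected patients are added. The interval printed in the plan, [3.07, 16.93], has half-width 6.93 and does not match 32 per group under this formula. That is a separate matter, and nothing here depends on it.

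**The case against.** The case for leaving the plan alone has real weight. The exclusion is not concealed: it is counted in the abstract and the sample size section, and stated beside the ITT definition. The withdrawal section promises to report these patients. Minimising selection bias promises the numbers screened, included and analysed, with differences explained, and a CONSORT flowchart. The named reasons, metastases and irresectability, mirror baseline exclusion criteria, so many of these patients will have disease that was found late. The most obvious arm-dependent route, technical difficulty with the robot, leads to conversion, and converted patients stay in their arm. Equal losses are expected. The trial is descriptive and tests no hypothesis, and an effect among resected patients is a legitimate target when planning a confirmatory trial.

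All of this stands, and it limits the point. It does not make the set ITT as the protocol defines it, and it does not supply an all-randomised analysis.

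Several stronger readings are tempting but not supported:
- **That the surgeon explores through the assigned arm's access.** No section says how exploration is done in each arm.
- **That the safety analysis omits these patients.** No safety population is named, details are left to an SAP that is not shown, and serious intraoperative complications are recorded on the day of surgery.
- **That early exit and V8 flatly contradict each other.** A patient could skip the intermediate visits and go to close-out. The trial flow chart, not shown here, may clarify this.
- **That the total pancreatectomy mismatch is a deliberate conflict of rules.** The withdrawal examples concern no resection, and the sample size text is an approximate count. It is a mismatch on literal reading.

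**Conclusion.** The point holds as one of definition, completeness and consistency. The primary set is a modified ITT restricted to randomised patients who had PD or total pancreatectomy. It is expected to leave out 16 of 80 patients (20%), and no analysis of all randomised patients is stated. The 20% comes from the plan's own counts and needs no further assumption.

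A reader might infer that the primary comparison is biased. The documents show only that bias is possible, because the exclusion follows randomisation and is made unblinded. The 0.16 to 2.5 point range rests on assumed numbers and severities and is not a prediction. Nor is a move from 10 to 8.0 evidence of bias: it is dilution under a different estimand. The narrower half-width with 40 per group is no argument either. If the effect did dilute to 8.0, the ratio of effect to half-width would fall from 10/9.80 = 1.02 to 8.0/8.77 = 0.91.

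Severity: should-fix. The trial is exploratory and descriptive, but its results are meant to inform the target population and sample size of a confirmatory trial, so the primary set should be named for what it is.

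**What to change.** 1. Rename the primary set 'modified ITT (randomised and resected)' and state its definition in one place.
2. Add a sensitivity analysis of the CCI in all randomised patients by assigned arm, with complications to POD 90 recorded at V8 for non-resected patients. Do not fill these patients in with the planned group-mean imputation: inserting an arm's mean leaves that arm's mean unchanged, so it would reproduce the modified ITT difference with false precision.
3. Report exclusions by arm and by reason. The planned flowchart already covers part of this.
4. Reconcile Withdrawal criteria, Sample size calculation, and Analysis variables and statistical methods on which operations lead to exclusion, including total pancreatectomy. Reconcile Withdrawal criteria and the analysis section, with Table 2, on whether excluded patients are followed and what V8 means for them.

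The cost is wording, one extra analysis and, if V8 is at present an immediate close-out, a new POD 90 contact for about 16 patients. The all-randomised estimate may be diluted and should be presented as answering a different question from the primary one.

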##### Minimising attrition bias

The trial is registered with the German Clinical Trials Register (*Deutsches Register Klinischer Studien*; DRKS00020407). To avoid the risk of selective reporting, the trial protocol with full information about endpoints and a detailed explanation of the planned statistical analysis is hereby published according to the Standard Protocol Items: Recommendations for Interventional Trials (SPIRIT) statement. The SPIRIT Checklist is provided as supplementary file 1. Statistical measures such as imputation will be taken to minimise the risk of bias due to incomplete outcome data.

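### Filling missing 90-day CCI values with the arm mean makes the primary 95% CI too narrow whenever any value is missing, and leaves the estimate unchanged

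*Protocol article*

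**What the plan says.** All of the following is in the protocol article, under Analysis variables and statistical methods, unless stated otherwise.

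- **Primary result:** "As a primary result, the 95% CI for the difference in the means between the two groups will be reported". On the method, "the 95% CI can be computed by means of the normal distribution".
- **Analysis set:** the ITT set "serves as the primary analysis set".
- **Missing primary endpoint:** "The primary endpoint is expected to be missing for a small number of patients, since it is objective and short term". For these patients "the primary endpoint is imputed using mean imputation based on the treatment group".
- **Sensitivity analyses:** worst-case and best-case scenarios, described as "Missing values of the primary endpoint will be imputed using the lowest and the highest value of the corresponding treatment group".
- **Per-protocol set:** "No missing data will be imputed in the PP set". This set also leaves out conversions and major protocol violations.
- **Purpose of imputation** (Minimising attrition bias): "Statistical measures such as imputation will be taken to minimise the risk of bias due to incomplete outcome data".

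The article names no variance correction, multiple imputation or observed-case analysis for the primary CI. It leaves further detail and the handling of data problems to a SAP, but it fixes the imputation method itself. It also describes all analyses as exploratory and descriptive.

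**The concern.** An arm mean put in place of a missing value carries no new information. It cannot move the arm mean, so the estimated difference is the same as if the patient had been left out. A standard CI formula nevertheless treats the filled-in patient as a real observation lying exactly at the mean. The sample size goes up, the sum of squares stays the same, and the standard error falls.

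The trial has no hypothesis test, so the CI for the mean difference is its main inferential output. A CI labelled 95% that covers less often misstates how precisely the difference is known. The rule also fails the aim given under Minimising attrition bias: compared with simply using the observed patients, it removes no bias and adds only apparent precision. The SD computed from the filled-in data is too small as well. This matters if that SD is carried into the planning of the confirmatory trial, for which the Discussion says the morbidity data are collected.

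**Working it through.** **Inputs.** From Sample size calculation: SD of the CCI about 20, 32 patients analysed per group, difference of interest 10. The normal-quantile CI is from Analysis variables and statistical methods. The number missing is not given. I assume 1, 2, 3 or 4 per arm of 32 (3.1%, 6.2%, 9.4%, 12.5%), the same in both arms.

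**The plan's own figure.** The article states an expected CI of [3.07, 16.93], a half-width of 6.93. The two-group formula gives 1.96 × 20 × √(2/32) = 9.80, so [0.20, 19.80]. The stated 6.93 equals 1.96 × 20/√32, the half-width for a single mean. That discrepancy is a separate matter. The complete-data reference used here is 9.80.

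**Effect of the rule.** Let k of n patients in an arm be observed.

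1. Arm mean after imputation: [k·x̄ + (n−k)·x̄]/n = x̄. The difference between arms is unchanged.
2. Sum of squares: the imputed values add zero, so it stays at (k−1)s².
3. SD after imputation: s·√[(k−1)/(n−1)].
4. Standard error of the arm mean after imputation: s·√[(k−1)/((n−1)n)]. The correct one is s/√k.
5. Ratio of reported to correct: √[k(k−1)/(n(n−1))], which is below 1 whenever k < n.

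Example with 2 missing: √[(30 × 29)/(32 × 31)] = √(870/992) = 0.936. The correct half-width is 1.96 × 20 × √(2/30) = 10.12. The reported one is 10.12 × 0.936 = 9.48. Coverage is 2Φ(1.96 × 0.936) − 1 = 93.4%.

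| Missing per arm | SE ratio | Correct half-width | Reported half-width | Coverage | SD ratio |
|---|---|---|---|---|---|
| 0 | 1 | 9.80 | 9.80 | 95.0% | 1 |
| 1 | 0.968 | 9.96 | 9.64 | 94.2% | √(30/31) = 0.984 |
| 2 | 0.936 | 10.12 | 9.48 | 93.4% | √(29/31) = 0.967 |
| 3 | 0.905 | 10.29 | 9.31 | 92.4% | √(28/31) = 0.950 |
| 4 | 0.873 | 10.48 | 9.15 | 91.3% | √(27/31) = 0.933 |

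**Simulation check** (100,000 runs, normal data, normal quantile). With 1, 2 and 3 missing per arm, the imputed CI covered 93.8%, 93.0% and 91.8%; the observed-case CI covered about 94.6% each time. With nothing missing, coverage was also 94.6%. That small shortfall comes from using the normal quantile with an estimated SD, not from imputation.

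Every reported half-width with missing data is below 9.80. Under this rule, losing patients yields a narrower CI than full follow-up would.

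**The case against.** The best defence is that the effect is small and nothing hinges on it. The protocol expects few missing values, all analyses are exploratory, there is no test or decision rule, and the point estimate is unaffected. At 1 missing per arm the half-width is off by 0.32 points, against a relevant difference of 10; at 2 it is off by 0.64. The plan also has sensitivity analyses and an unimputed per-protocol set. This limits the importance of the point but does not remove it. The lowest- and highest-value scenarios test where the estimate might lie; they are also single imputations and do not correct the primary CI. The per-protocol set drops conversions, so it is not an observed-case version of the ITT analysis.

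Four stronger readings are tempting, and the document does not support them:

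- **The primary CI will fall short of 95% coverage whatever happens.** The shortfall depends on a missing rate that is not stated; with complete data the rule does nothing.
- **Recorded complications will be overwritten.** One might picture a patient with a severe complication at POD 8, lost before POD 90, who is set to the arm mean. The CCI is assessed at several visits (Table 2), and the article does not say whether partial follow-up counts as missing. The SAP may settle this.
- **The confirmatory trial will be undersized.** The Discussion says the morbidity data will support its sample size calculation, not that the imputed SD will be used.
- **Multiple imputation is required.** For a few patients in an exploratory trial it is an option, and a version bounded by the CCI already accrued takes real modelling effort.

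**Conclusion.** The point holds as a flaw in the rule as written. Its direction is certain: any missing value makes the SD and the primary CI too small, with no gain in the estimate over the observed cases. Its size is conditional. Under SD 20, 32 per arm and equal missingness in both arms, the CI is about 3% too narrow with 1 missing per arm, 6% with 2, 10% with 3 and 13% with 4, with coverage falling from about 94.2% to 91.3%. The SD is about 3% low with 2 of 32 missing. At the low missing rate that the protocol expects, the effect is modest. It is still worth correcting, because the CI is the primary result and the repair costs almost nothing.

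**What to change.** 1. Delete arm-mean imputation from the primary analysis. Report the observed-case difference in the ITT set with its own standard error. The estimate is the same, and the CI is valid if missingness is unrelated to outcome within each arm; state that assumption.
2. Keep the lowest- and highest-value scenarios as sensitivity analyses for departures from that assumption.
3. Report the number missing per arm and the SD from observed patients only, so that any use of the SD in planning the confirmatory trial is not biased low.
4. State how patients with partial follow-up are handled. If they would count as missing, their recorded complications should not be replaced by the arm mean.
5. Optionally, use multiple imputation by arm, drawing on the CCI already accrued.

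Items 1 to 4 need only a change of wording and simple programming. They can go into the SAP before database closure, documented as a departure from the published text. No extra patients or visits are needed. The only downside is a slightly wider CI.
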